## Methods/design

### Design and overview

POISE is a prospective multicentre observational study with study registration number ACTRN12608000459325. The primary aim of POISE is to determine if modifiable early (within 28 days of stroke) psychosocial factors are associated with people's ability to return to work one year after stroke. The secondary aim is to determine the economic impact of not returning to work for younger stroke survivors and their families. Participants are recruited as soon as possible after stroke from the Stroke Services New South Wales (SSNSW) network. Stroke status is verified by the recruiting centre staff and baseline demographic and clinical data are collected. Interviews are conducted by centrally located trained interviews at 28 days, 6 and 12 months.

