### Study population

Recruitment began across the Stroke Services New South Wales (SSNSW) (see Table 2) network in Australia on 1 October 2008, and will continue until 440 participants are recruited.

Men or women aged over 17 years and less than 65 years of age will be eligible to participate in the study if they fulfil all of the following criteria:

1. Recent (within 28 days) acute stroke, defined according to the WHO standard diagnostic criteria of "rapidly developing clinical signs of focal (at times global) disturbance of cerebral function lasting more than 24 hours...with no apparent cause other than vascular origin",[30] this definition includes all main pathological subtypes, ischaemic stroke, primary intracerebral haemorrhage and subarachnoid haemorrhage (SAH) but excludes cases of silent stroke (detected by neuroimaging without appropriate clinical features) and transient ischaemic attack, and

2. Able to speak English sufficiently to respond to study questions, and

3. They or their proxy are able to provide written informed consent. (Participants with receptive aphasia or a severe language disorder or cognitive impairment (as determined by their treating clinician) are eligible to take part in the study provided their proxy is able to provide written informed consent and complete the assessments on the participant's behalf), and

4. Consent is given to contact the participant's general practitioner if necessary.

Study co-ordinators at each site review the medical records of potential participants to determine eligibility. Each recruiting site maintains a log of every eligible stroke patient who is offered participation in the study. The logs contain the initials and date of birth of the eligible patients and the date they were screened for participation in the study. Participants are asked to consent to the abstraction of information about their stroke from medical records, assessments at 28 days (baseline), six months and one year (primary endpoint), and for the participant's general practitioner (GP) to be contacted by research staff if necessary.

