### Assessments and data collection

The detailed schedule for data collection is shown in Table 1.

**Table 1 T1:** Schedule of assessments in the POISE study

**Participant Assessment ^a^**	**Screening**	**28 days^ b^**	**6 month**	**12 month**
Initials	X			

Date of birth	X			

Sex	X			

Inclusion criteria	X			

Contact information	X			

*Interview Characteristics*				

Method of assessment		X	X	X

Participant or proxy		X	X	X

Alive at scheduled time of assessment		X	X	X

Telephone Interview for Cognitive Status (TICS)[31]		X	X	X

*Demographic characteristics*				

Born in Australia		X		

Years lived in Australia		X		

Language other than English spoken at home		X		

Marital status		X		

Number of financially dependent children		X		

Social/financial living status		X	X	X

Height/Weight		X		

Highest educational qualification		X		

Pre-stroke social activities (Frenchay Activities Index)[32]		X		

*Pre-stroke Medical History*				

Smoking status		X		

Alcohol consumption: Audit Alcohol Use Disorders Identification Test (AUDIT-C)[33]		X		

Activity restricting illness		X		

Comorbidities		X		

Psychotropic medications		X		

Participated in talking therapy for mood		X		

*Current Medical History*				

Psychotropic medications			X	X

Participated in talking therapy for mood			X	X

*Pre-stroke Work Status*				

Lifetime occupation		X		

Most recent occupation		X		

Duration of most recent job		X		

Main income earner		X		

Union/organisation member		X		

Own own business		X		

Hours of paid, unpaid, domestic & volunteer work^c^		X		

Mode of travel to work		X		

Legally able to drive		X		

Drive for work		X		

Modified Job Content Questionnaire (JCQ)[35]		X		

Student		X		

*Current Work Status*				

Want to return to work		X	X	X

Returned to work: part time, full time		X	X	X

Returned to work: same conditions, altered conditions		X	X	X

Hours of paid, unpaid, domestic & volunteer work^c^		X	X	X

Legally able to drive		X	X	X

Mode of travel to work		X	X	X

Advised to stop driving since stroke		X	X	X

Driving since stroke		X	X	X

Student		X	X	X

*Pre-stroke household economics*				

Dependent on other household member for ADL		X		

Received carer payment		X		

Experiencing financial hardship		X		

Received financial assistance to meet costs		X		

Received government benefits		X		

Private health insurance		X		

Income protection insurance		X		

Household weekly income		X		

*Post-stroke household economics*				

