Dependent on other household member for ADL		X	X	X

Received carer payment		X	X	X

Experiencing financial hardship			X	X

Received financial assistance to meet costs			X	X

Received government benefits			X	X

Private health insurance			X	X

Income protection insurance			X	X

Household weekly income			X	X

*Post-stroke social activities*				

Frenchay Activities Index[32]			X	X

*Post-stroke psychosocial Disability*				

WHO Disability Assessment Scale (WHODAS)[36]		X	X	X

*Post-stroke mood*				

Hospital Anxiety and Depression Scale (HADS)[37]		X	X	X

*Post-stroke sleep and vitality*				

Trouble sleeping, early waking, daytime tiredness		X	X	X

Snoring		X	X	X

SF-36 Vitality Scale[38]		X	X	X

*Rehabilitation*				

Physical, vocational, job assistance		X	X	X

*Social contacts*				

Close friends		X	X	X

Able to borrow money		X	X	X

Perception of social support		X	X	X

*Overall*				

Affect of stroke on life		X	X	X

^a ^Or proxy if applicable

^b ^Baseline assessment conducted at 28 days post-stroke

^c ^Questions modified from questions 34–51 of the Australian Bureau of Statistics 2006 census relating to jobs and work

Contact information, basic demographic characteristics and stroke information (subtype and severity) are collected by study co-ordinators at each site, immediately following consent, and entered into the internet-based case report forms (eCRFs).

At 28 days after stroke, consented participants are contacted, via telephone, by centrally located interviewers. This assessment includes collection of detailed demographic data, and pre-stroke medical history (prior vascular disease, pre-stroke disorders, other co-morbid conditions), social activities, work status and household economic status. At 28 days, six and 12 months after stroke information is also collected on current work, social and financial living status, use of interventions for mood problems, work status, driving status, household economics, social activities, psychosocial disability, mood, sleep, rehabilitation, social contacts and the overall affect of stroke. Each assessment begins with an assessment of cognitive status.

Specific questionnaires used include:

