The *Telephone Interview for Cognitive Status *(TICS-M)[31] has been validated for assessment of cognitive function for research purposes. Scores are normally distributed and it is sensitive to change in cognitive performance. The 13-item TICS-M test includes orientation, recent and delayed memory, attention and comprehension assessments with a maximum score of 39. As the TICS-M is administered via the telephone it can be used in people with visual difficulties or poor hand-eye co-ordination.

The *Frenchay Activities Index *(FAI)[32] is a 15-item questionnaire specifically developed to measure social function in people with stroke. The FAI covers mainly domestic, leisure, social and work activities, and uses a four-point frequency scale ranging from 'never' to 'frequent' with total scores ranging from 0 (no activities) to 45 (full activities).

The *Alcohol Use Disorders Identification Test *(AUDIT-C)[33] uses three questions to collect information from the participants on 'at-risk' alcohol consumption. Individual question scores range from zero to four. At risk alcohol consumption is indicated by a total score of five or more for males or four or more for females. A single simple question is used to determine current *smoking *status.

Information on paid and unpaid work is collected using modified versions of questions 34–51 of the *Australian Bureau of Statistics 2006 Census *relating to jobs and work. [34] 2006 was the first year that questions on unpaid domestic work, caring for someone with a disability, looking after a child without pay and voluntary work were included in the Australian census. The same definitions and categories are used in POISE, where appropriate. The average number of hours of paid and unpaid work performed per week over the previous 12 months will be calculated as per the Australian census.

Participants are asked to indicate whether, and in what capacity, they have *returned to work *(paid and unpaid): same job, similar job, different job, average number of hours worked per week, not returned to work. The date of return to partial or full-time work is recorded. Questions are asked about changes in income and whether any government benefits (sickness, disability, or unemployment) or health-insurance benefits were received.

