### Statistical considerations

To test the univariate association between depression at 28 days and return to work status at 12 months, a chi-squared test will be conducted. Assuming a conservative prevalence of depression of 25% and an overall return to work of 50% (as found in the ARCOS study[2]), then to detect a relative risk of returning work of 0.5 amongst the depressed we will require 150 participants. We will aim to recruit 220 participants to allow for loss to follow up, potential clustering effects, missing data and to provide sufficient numbers for multivariate modelling. We intend to examine return to paid and unpaid work separately so require a total sample of 440 participants.

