### Statistical analysis

We will conduct a logistic regression model with 'returned to work' as a dichotomous response variable and a combination of *a priori *and univariately associated variables described in the 'assessments and data collection' as explanatory variables. The associations with the continuous outcome of the number of quality hours of work returned to will be modelled using linear regression.

The time of first return to work will be modelled by all the other explanatory variables using a Cox regression (survival analysis) model. These models will be fitted on two subsets of data: paid and unpaid work. The same predictor variables will be tested in each model and coefficients in the models for paid and unpaid work will be compared in relation to their size and significance to see how different variables affect return to paid and unpaid work, and time to return to paid and unpaid work.

Economic hardship will be constructed as a dichotomous variable where a reported inability to make any one of the payments posed to respondents will be classed as a case of economic hardship. A logistic regression model will be fitted to determine the extent to which variables affect the risk of this outcome as outlined above. Estimates of average production losses associated with cases of stroke, and stroke with depression as a complication, will be estimated based on an analysis of average amounts of time off work multiplied at the various rates for estimating production gains/losses outlined above. Adjustment for production losses caused by return to work at impaired capacity will be estimated. A sensitivity analysis will be conducted on this economic outcome involving the differing valuation methods and scenarios regarding the level of impairment and its impact on production.

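### The Cox model of first return to work, and the logistic model if it means ever returned, relate 28-day predictors to returns that may already have happened by day 28

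*Protocol article*

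**What the plan says.** All references are to the protocol article.

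- **Aim** (Design and overview): whether "modifiable early (within 28 days of stroke) psychosocial factors are associated with people's ability to return to work one year after stroke".
- **When predictors are measured** (Table 1, footnote b): "Baseline assessment conducted at 28 days post-stroke". Table 1 first schedules the depression and anxiety scale, the disability scale and the vitality scale at that interview.
- **Work status at the same interview** (Table 1, Current Work Status): the item "Returned to work: part time, full time" is marked at 28 days as well as at 6 and 12 months.
- **Dates** (Assessments and data collection): "The date of return to partial or full-time work is recorded". No earliest date is set.
- **Eligibility** (Study population): "Recent (within 28 days) acute stroke, defined according to the WHO standard diagnostic criteria". No criterion removes people who have already resumed work.
- **Time-to-event model** (Statistical analysis): "The time of first return to work will be modelled by all the other explanatory variables", by Cox regression, fitted separately for paid and unpaid work. No time origin, landmark, delayed entry or exclusion is given.
- **Binary analyses**: Statistical considerations plans a chi-squared test of depression at 28 days against work status at 12 months. Statistical analysis plans a logistic model of having returned to work, without saying whether this means ever returned or working at 12 months.

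**The concern.** A predictor should be known before the event that it predicts. The schedule asks about return to work at the very interview that first measures mood, so the design itself allows for returns before the predictor exists. In a model of first return, such a person contributes an event that is explained by a score taken later. If being back at work improves mood, early returners will score as less depressed because they have returned, and the model will read this as depression delaying return.

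Unpaid work may be the more exposed outcome. It includes domestic work and child care, which could plausibly resume soon after discharge, although the article gives no figures on this.

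At stake is the claim that the study identifies targets for early intervention. An association produced partly by return acting on mood would point to a target that treatment may not move.

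**Working it through.** **Order of events.** The Cox outcome is first return. If the clock starts at stroke, a return on day 20, say, is an event explained by a score taken on day 28. If it starts at the 28-day interview, the same person has a negative event time and needs a rule. Under either origin, the stated outcome and predictors do not fit together for early returners.

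**The plan's own figure.** The article assumes 25% depressed, 50% returning overall and a relative risk of 0.5, and asks for 150 participants, raised to 220 for each type of work. The implied rates are 0.5 / (0.75 + 0.25 × 0.5) = 57.1% in the non-depressed and 28.6% in the depressed. At two-sided 5%, without continuity correction, this needs 124 participants for 80% power and 164 for 90%; 150 gives 87.6%. The article states neither alpha nor power, so 150 is plausible but cannot be confirmed. The present point does not depend on it.

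**Size of the possible bias.** From the article: 25% depressed, 50% returned by 12 months, 220 participants (55 depressed, 165 not). Assumed: *e*, the share back by day 28; *r*, the prevalence of depression in early returners divided by that in the rest; no effect of depression on any return after day 28; every early returner counted as returned. The outcome is any return by 12 months.

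- Prevalence in those not yet back: q = 0.25 / [(1 − e) + e·r]; in early returners: r·q.
- Later return among those not yet back: h = (0.5 − e) / (1 − e).
- Return in the depressed: R1 = [e·r·q + (1 − e)·q·h] / 0.25.
- Return in the non-depressed: R0 = (0.5 − 0.25·R1) / 0.75.

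Worked case, e = 0.20 and r = 0.5: q = 0.25/0.90 = 0.278 and h = 0.30/0.80 = 0.375. R1 = (0.2 × 0.139 + 0.8 × 0.278 × 0.375)/0.25 = 0.444. R0 = (0.5 − 0.111)/0.75 = 0.519. The relative risk is 0.444/0.519 = 0.86.

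| e | r | R1 | R0 | Spurious RR | Chance of a significant harmful result (nominal 2.5%) |
|---|---|---|---|---|---|
| 5% | 0.5 | 0.487 | 0.504 | 0.97 | 4.1% |
| 10% | 0.5 | 0.474 | 0.509 | 0.93 | 6.5% |
| 20% | 0.5 | 0.444 | 0.519 | 0.86 | 15.5% |
| 20% | 0.25 | 0.412 | 0.529 | 0.78 | 32.5% |
| 25% | 0.25 | 0.385 | 0.538 | 0.71 | 50.7% |

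These are crude relative risks for a binary outcome. They illustrate direction and order of size; no Cox hazard ratio was computed.

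**Power under a landmark.** Keep 25% depressed and a relative risk of 0.5 among those not yet back, two-sided 5%, starting from 220. The rate in the non-depressed is h / 0.875.

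| e | Participants left | h | Power |
|---|---|---|---|
| 0% | 220 | 0.500 | 97% |
| 5% | 209 | 0.474 | 94% |
| 10% | 198 | 0.444 | 90% |
| 20% | 176 | 0.375 | 74% |
| 25% | 165 | 0.333 | 63% |

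This too is a comparison of two proportions, with nothing taken off for loss to follow-up.

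**The case against.** The strongest reply is that a condensed article may leave the time origin and the handling of pre-baseline events to the full protocol or analysis plan. That stands as far as the silence goes: an unstated origin is no finding in itself. It does not remove the mismatch, because neither possible origin makes first return compatible with predictors measured at day 28 for those already back.

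Several stronger readings are tempting, and the document does not support them.

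- *Time is counted from stroke onset.* A reader might infer this, but no origin is given, and the 28-day interview is called the baseline.
- *Every model is affected.* The planned test reads "To test the univariate association between depression at 28 days and return to work status at 12 months, a chi-squared test will be conducted". There the depression score precedes the outcome, and early return is at most an earlier state that may confound. The economic-hardship model has a different outcome. Predictors that describe the pre-stroke period, such as education or previous job content, cannot be caused by return.
- *The first 28 days are immortal time.* The need for a 28-day interview applies equally to depressed and non-depressed participants, so neither group gains event-free time.
- *Reverse causation is shown.* It is only possible. A milder stroke could produce both early return and better mood. Stroke severity is collected and could enter the multivariable models, whereas the relative risks above are crude.

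A further objection carries weight. Restricting to people still off work at day 28 changes the population and conditions on something that early mood may itself have influenced. Where the bias would be largest, the loss of power is largest too. This is why the landmark should not replace the 12-month status analyses.

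**Conclusion.** The point holds for the Cox model of time to first return, and for the logistic model if its outcome means ever returned. As written, these let a depression score taken at day 28 explain returns that may have come before it. The likely direction is to make depression look harmful.

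The bias is small if few are back early (relative risk about 0.97 at 5%) and material at about 20% or more (about 0.78 to 0.86 at 20%). The article gives neither the share back by day 28 nor their prevalence of depression, so these figures are a range under stated assumptions and not an estimate for this study. They also assume that every early returner counts as returned and that depression has no effect on later return.

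The test of depression at 28 days against status at 12 months does not have this fault.

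**What to change.** 1. **Cox model, and any ever-returned model:** start follow-up at the 28-day interview and include only participants who have not yet returned to that type of work, paid and unpaid taken separately. Describe early returners as their own group. Give the all-participant model as a sensitivity analysis.
2. **Chi-squared and logistic analyses of 12-month status:** keep all participants as planned and define the outcome as working at 12 months. Add a sensitivity analysis that leaves out those already back at the 28-day interview.

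The work-status items and return dates are already scheduled, so the change is one of wording and needs no new data. The price is fewer participants and events in the landmark models. From 220, power for the relative risk of 0.5 falls from about 97% with no early returns to about 90% if 10% are back early and about 74% if 20% are. The rule is best fixed before the results are seen.

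### Predictors of return to paid and unpaid work are to be contrasted by the size and significance of separately fitted coefficients, which neither tests a difference nor gives its uncertainty

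*Protocol article*

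**What the plan says.** The Statistical analysis section of the protocol article describes a logistic model for having returned to work and a Cox model for time to first return. It then states: "These models will be fitted on two subsets of data: paid and unpaid work". On predictors it says "The same predictor variables will be tested in each model". It goes on to say that "coefficients in the models for paid and unpaid work will be compared in relation to their size and significance", and gives the purpose: "to see how different variables affect return to paid and unpaid work, and time to return to paid and unpaid work".

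The Statistical considerations section sizes one work type from a chi-squared test of 28-day depression against 12-month return to work. It assumes 25% depressed and 50% returning overall, and says that "to detect a relative risk of returning work of 0.5 amongst the depressed we will require 150 participants". Recruitment is then raised: "We will aim to recruit 220 participants to allow for loss to follow up, potential clustering effects, missing data". That figure is doubled to 440 because paid and unpaid work are to be examined separately. No alpha, sidedness or power is given, and no sample size is given for a contrast between the two work types.

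**The concern.** A predictor can be significant in one model and not in the other purely by sampling variation, even when its true effect is the same in both. Comparing the size of the coefficients by eye does not resolve this, because nothing in the plan says how large a gap chance would produce. What is needed is an estimate of the difference with its standard error, and the article provides for neither.

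This is not a detail left to an analysis plan that is not shown. The article names its method of comparison, and the method named does not answer the question it is given.

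At stake is any statement that a factor matters for paid but not unpaid work, or the reverse. The Background section on existing studies criticises earlier work for not separating the two, and the Discussion expects the results to point to intervention targets. A false contrast could direct vocational strategies at the wrong group.

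**Working it through.** **Inputs.** From Statistical considerations: 25% depressed, 50% return overall, relative risk 0.5, 150 required, 220 recruited per work type. Assumed because the article is silent: two-sided 5% and independent subsets. Assumed for illustration: weaker predictors with odds ratios 0.4–0.7, 25% exposed, 55% return in the unexposed.

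**Implied proportions.** With x the return rate in the non-depressed, 0.25(0.5x) + 0.75x = 0.50, so x = 0.571, and the depressed rate is 0.286. The odds ratio is (0.286/0.714)/(0.571/0.429) = 0.30.

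**The plan's 150.** Without alpha or power it can only be bracketed. With unpooled variance, two-sided 5% and 90% power:

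N = 4(1.96 + 1.28)² × [0.286×0.714 + (0.571×0.429)/3] / 0.286² = 147.

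The pooled formula gives 124, 140 and 164 at 80%, 85% and 90% power. So 150 is plausible, and the point does not depend on it.

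**Chance of discordant significance when the true effects are equal.** If each model has power p and the subsets are independent, the chance that exactly one is significant is 2p(1−p). In general:

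- p = 0.90: 2 × 0.90 × 0.10 = 18%
- p = 0.80: 32%
- p = 0.50: 50%
- no effect in either (p = 0.05): 9.5%

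**At the plan's design effect.** For a Wald test of the log odds ratio, |log 0.30| = 1.204.

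- 220 analysable (55 exposed, 165 not): SE = √[1/(55×0.286×0.714) + 1/(165×0.571×0.429)] = 0.337; z = 3.57; power = Φ(3.57 − 1.96) = 0.946; discordance = 2 × 0.946 × 0.054 = 10%.
- 150 analysable: SE = 0.409; z = 2.95; power = 0.838; discordance = 27%.

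Simulation (200,000 runs) gives 7% at 220 (power 96%) and 23% at 150 (power 87%). The pooled chi-squared approximation gives power 96.8% and 87.6%, hence 6% and 22%. The approximation used therefore moves the figures a little; about 7–10% and 22–27% is a fair summary.

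**Weaker predictors (simulated discordance, equal true effects).**

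| Odds ratio | 220 per subset | 150 per subset |
|---|---|---|
| 0.4 | 30% | 46% |
| 0.5 | 49% | 49% |
| 0.6 | 46% | 38% |
| 0.7 | 32% | 25% |

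**Correlation.** If the two estimates were positively correlated (assumed 0.3–0.5), discordance at 80% power would fall from 32% to 27–23%.

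**A direct test.** With z = (b₁ − b₂)/√(SE₁² + SE₂²), the simulated rate of falsely declaring a difference was about 4.6–5.0% in every one of these scenarios.

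**What a direct test can detect.** With SE 0.33 in each subset, the SE of the difference is 0.33√2 = 0.467. For a two-fold ratio of odds ratios, power = Φ(0.693/0.467 − 1.96) = 32%; with SE 0.319 it is 34%. For a three-fold ratio it is 65% (SE 0.33). The 95% CI for the ratio extends by a factor of exp(1.96 × 0.467) = 2.5 each way.

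These figures are for the logistic models. The same logic applies to the Cox models, for which the article gives too little to compute.

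**The case against.** The strongest reply is that the article states no decision rule. It compares size as well as significance, and the sentence can be read as describing two sets of results side by side. This stands in part: the error rates above belong to a reading of discordant p-values, not to a rule the plan sets out, and the plan attaches no 5% level to this contrast. It does not remove the defect, because a comparison of sizes without an interval is equally uninformative about chance.

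Second, for depression at the full design effect with all 220 analysable, false discordance is modest. That also stands. But 220 already allows for loss and missing data, so the analysable number may be nearer 150, and many candidate predictors may be weaker.

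Third, a direct test has low power. True, and it limits what these data can show by any method.

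A reader might go further and infer any of the following, none of which the documents support:

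- *That many participants do both kinds of work, so the estimates are correlated.* Hours of both kinds are recorded, but no overlap is given. Two subsets and 2 × 220 = 440 fit separate groups at least as well.
- *That job-specific items such as the Job Content Questionnaire would remove people from a complete-case unpaid model.* The logistic model takes a priori and univariately associated variables, not every Table 1 item. The questionnaire is listed as modified, several items concern the most recent job, and complete-case analysis is nowhere specified.
- *That the design gives about 88% power.* That figure follows only from assumed two-sided 5% and 150 analysable.
- *That the sample was doubled to contrast the two work types.* It was doubled to examine each separately.

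**Conclusion.** The point holds. The stated method does not test whether predictors act differently on paid and unpaid work, and it gives no uncertainty for the difference. If discordant significance is taken as a difference, the chance of a false contrast per predictor runs from about 7–10% in the most favourable case (design effect, 220 analysable) through 22–27% (design effect, 150 analysable) to about 30–50% (odds ratios 0.4–0.7, 220 analysable). These figures rest on two-sided 5%, 25% exposed, independent subsets and, for the last range, assumed effect sizes.

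It is a should-fix. A reader might take it to undermine the whole study, but the Design and overview section sets two aims: early psychosocial factors and return to work at one year, and the economic impact of not returning. The paid-versus-unpaid contrast is neither, and both aims can be met without it.

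**What to change.** For predictors defined in both groups, fit one joint model with predictor-by-work-type interactions: logistic for return to work, and Cox stratified by work type for time to return. Use participant-clustered standard errors if any participant contributes to both subsets. Report the ratio of odds ratios or hazard ratios with its 95% CI, and rest any statement that predictors differ on that interval and not on one p-value falling below 5% while the other does not. The separate models can stay as the description of each outcome.

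The cost is a few sentences of analysis-plan wording and some programming, with no new data. The downside is that few differences will be shown, given power of about 32–34% for a two-fold ratio of odds ratios at 220 per subset. The report should therefore say that failing to show a difference is not evidence that the effects are similar.
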